## Abstract

**Background:**

Childhood obesity has reached epidemic proportions in developed countries. Sedentary screen-based activities such as video gaming are thought to displace active behaviors and are independently associated with obesity. Active video games, where players physically interact with images onscreen, may have utility as a novel intervention to increase physical activity and improve body composition in children. The aim of the Electronic Games to Aid Motivation to Exercise (eGAME) study is to determine the effects of an active video game intervention over 6 months on: body mass index (BMI), percent body fat, waist circumference, cardio-respiratory fitness, and physical activity levels in overweight children.

**Methods/Design:**

Three hundred and thirty participants aged 10–14 years will be randomized to receive either an active video game upgrade package or to a control group (no intervention).

**Discussion:**

An overview of the eGAME study is presented, providing an example of a large, pragmatic randomized controlled trial in a community setting. Reflection is offered on key issues encountered during the course of the study. In particular, investigation into the feasibility of the proposed intervention, as well as robust testing of proposed study procedures is a critical step prior to implementation of a large-scale trial.

**Trial registration:**

Australian New Zealand Clinical Trials Registry ACTRN12607000632493

## Background

Childhood obesity has reached epidemic proportions in developed countries [1]. In New Zealand (NZ) almost one third (31%) of children aged 5–14 years old are overweight or obese [2]. The causes of obesity are multi-factorial. Research evidence points toward an imbalance between energy intake (food consumed) and energy expenditure (physical activity) [3]. Current lifestyles and environments are thought to discourage regular physical activity and encourage sedentary behaviors in children [4,5]. In particular, sedentary screen-based behaviors (such as television watching, video game play, and computer use) are thought to displace physical activity and are independently associated with obesity [6] and other adverse health outcomes such as hypertension [7]. In NZ, television watching is the most popular leisure time activity [8]; data from multiple sources [2,9,10] show that NZ children watch more than two hours of television on average per day. Video game playing is also pervasive. A report from the United Kingdom found that 91% of children played three or more gaming formats (or platforms), with video console games the preferred choice. For 11–16 year old children, 74% played 3–7 times per week, with an average duration of 1.9 hours (per session). Similar results have been reported for 6–10 year olds [11]. This video game usage mirrors that seen in NZ and other countries [12,13]. A recent review [14] found a positive association between non-television screen viewing (e.g., video games, computer games) and obesity. Similarly, a positive association was reported between time spent playing screen games and obesity after controlling for television watching.

To date, interventions aimed at decreasing obesity in children have been largely unsuccessful. A recent Cochrane systematic review of trials to prevent obesity [15] found 22 studies; ten long-term (at least 12 months) and 12 short-term (12 weeks to 12 months) that investigated a variety of single or multifaceted interventions [16]. Of the long-term studies, six combined dietary and physical activity interventions [17-22]. Five of these studies resulted in no difference in overweight status between groups. Two long-term studies used physical activity as the sole intervention [23,24]. Of these, a multi-media approach appeared to be effective in preventing obesity. Four short-term studies used physical activity as the sole intervention [25-28], and two [25,28] resulted in minor reductions in overweight status in the intervention group. The other eight short-term studies combined advice on diet and physical activity, but none had a significant impact.

The authors of this review highlighted a number of significant design flaws which marred the majority of studies; 1) being underpowered and/or poorly designed given the complexity of the intervention and outcomes sought; 2) many were short term in duration; and 3) lack of environmental influence that would affect the sustainability of the intervention. Despite these limitations, the authors concluded that strategies to increase physical activity and reduce sedentary behavior may be fruitful in preventing overweight and obesity in schoolchildren and that further well-designed randomized controlled trials are required [16].

Turning off television has been advocated as a population health strategy [10,28]. However, television and computer games offer a distraction for children at busy times in a parent's day and thus reducing time spent in such sedentary activities constitutes a major challenge. A novel strategy might be to provide popular active alternatives to displace sedentary activities [29]. A new generation of active video games ('exer-gaming') such as Sony PlayStation^® ^EyeToy™ and Nintendo Wii™ provide the potential to turn a traditionally sedentary behavior into a physically active one. During these games, players interact physically (using arm, leg, or whole-body movement) with images onscreen in a variety of activities such as sports (e.g., football, boxing, martial arts) and other activities (dancing, washing windows etc). Games are dependent on player movement, and this active component replaces the largely sedentary hand controller of traditional video games whereby button pushing is used to control the game.

Numerous research studies have been conducted to quantify the energy cost of active video games. Without exception, playing active video games have been shown to elicit greater energy expenditure compared to rest and traditional non-active video games, as well as other common sedentary activities such as TV watching [30-32]. Overall, the energy expenditure associated with playing these active video games is similar in intensity to traditional physical activities such as walking, jogging, and cycling, approximately 3–6 Metabolic Equivalents (METS), which are multiples of resting metabolic rate. Recently, active video games have been considered in intervention research. Four small (*n *ranged from 15–60), short-term studies [33-36] have been conducted, of which three reported improvements in physical activity level among children over periods of 4–12 weeks. The fourth study [36] found no effect on physical activity. All studies were of short duration (12 weeks maximum) and thus were unable to provide insight into the sustainability of this intervention and the possible impact on other important variables such as body mass and physical fitness.

Taken together, these findings indicate that active video games are a promising and novel approach to promote physical activity in children. A large, methodologically sound randomized controlled intervention trial is required to determine definitively the long-term effect of active video games on children's physical activity and other outcomes. This paper describes the design and conduct of the eGAME (Electronic Games to Aid Motivation to Exercise) study, which will determine the effects of an active video game intervention over six months on: body mass index (BMI), body weight, percentage body fat, waist circumference, cardio-respiratory fitness, and physical activity levels in overweight NZ children. It was hypothesized that playing 30 minutes of active video games per day over a 6 month period could improve body composition, cardio-respiratory fitness, and physical activity levels in overweight children.

## Methods/Design

### Feasibility studies

The main eGAME study followed a three phase feasibility study conducted in 2005/2006. Phase one consisted of focus groups with children and adults to determine attitudes and preferences to video game play. All children enjoyed active video games, however older children (14 years) preferred traditional non-active games. Adults preferred that children performed physical activity in more traditional outdoor activities but said they would prefer active video game play to the non-active video games. For phase two a laboratory study was conducted to quantify the energy expenditure associated with playing active (Sony EyeToy^®^) and non-active video games [32]. Overall, results showed that energy expenditure was significantly greater in the active video games compared to rest and non-active gaming conditions. The exercise intensity of the active video games ranged between 3.2 and 6.8 child-specific METs.

In phase three a pilot randomized controlled trial (RCT) was conducted to determine the effect of active video game play on physical activity levels [33]. Twenty children aged 10–14 years were randomly assigned to either receive an active video game intervention (n = 10), or no change (control; n = 10). Over the 12 week intervention period, the average time spent in all physical activities (measured by accelerometry) was higher in the active video game intervention group compared to the control group.

### Design

The eGAME study is a standard two-arm parallel RCT. Eligible children are randomized to either an active video games intervention or control (no change) following baseline assessment. The randomization is via a computerized central randomization service and stratified by sex and ethnicity. The study manager and research assistants are responsible for enrolling participants and group assignment. Ethical approval for the study was granted by the Northern Y Ethics Committee (reference: NTY/07/09/099).

### Participants

Children aged 10–14 years living in the greater metropolitan Auckland area, who are overweight (according to the Cole international cut-offs for child obesity) [37], play ≥ two hours of video games per week, and have no contraindications to perform physical activity are eligible to participate in the study. Participants are required to own a PlayStation^® ^2 or 3 gaming console but not the EyeToy™ or Dance Mat technology. Only one child per household is eligible to take part.

### Sample size

A sample size of 330 participants was estimated to provide at least 90% power at 5% level of significance (two-sided) to detect a 0.8 kg/m^2 ^difference in change in BMI from baseline to the end of intervention period between the two groups, assuming a standard deviation (SD) of 2.0 kg/m^2 ^and allowing for 20% loss to follow up. The estimated difference in BMI assumed a difference in weight between groups at the end of intervention of approximately 2 kg with an average height of 1.58 m. This sample size also provides at least 90% power to detect an estimated 3–5 ml/kg/min difference in peak VO_2max _assuming a SD of 7 ml/kg/min. Recruitment of equal numbers of Māori (indigenous people) (n = 110), Pacific, (n = 110) and non-Māori/non-Pacific (n = 110) participants would provide nearly 80% power for the sub-group analysis under the same assumptions.

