### Statistical analysis

Statistical analyses will be performed using SAS version 9.1.3 (SAS Institute Inc. Cary NC) and R version 2.8.1 (R Foundations for Statistical Computing). All statistical tests will be two-tailed and a 5% significance level maintained throughout the analyses. All treatment evaluations will be performed on the principle of Intention to Treat (ITT). Repeated measures analysis using the mixed model will be carried out to evaluate the effect of intervention on change from baseline measures at 12 and 24 weeks, adjusting for baseline outcome measure, age (in years), sex (male/female), and ethnicity (Māori/Pacific/nMnP). With roughly equal number of Māori, Pacific and non-Māori non-Pacific participants, appropriate sub-group analysis will be carried out for each ethnicity if there is a significant overall treatment effect.

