### Recruitment of indigenous and ethnic minority populations

Researchers have typically struggled to recruit sufficient participants from indigenous and ethnic minority populations to allow for sub-analyses to be undertaken by ethnicity. The eGAME study aims to recruit equal numbers of Māori, Pacific, and nMnP participants, and proactive steps were taken to maximize recruitment in Māori and Pacific populations.

Consultation with Māori and Pacific communities during the focus groups provided useful feedback on design of the main study. A specialized Māori/Pacific recruiter was contracted to assist with recruitment of these populations and consult on cultural issues relevant to the conduct of the research. As a result, additional recruitment sites were set up in the greater Auckland area where a large number of Māori and Pacific resided, to improve access of these populations to the study. Furthermore, some study processes were modified to improve cultural appropriateness. For example, at one study site the screening phone call was changed to a face-to-face visit between study staff and the potential participant and their family, the preferred mode of communication for Māori and Pacific populations. The Māori/Pacific recruiter maintained regular contact with participants throughout the course of their involvement with study. Despite these steps, recruitment of Māori and Pacific children remains a challenge. At the time of submission of this manuscript, the eGAME sample comprised 17% Māori and 27% Pacific participants, below the target of 33% for each.

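### Sub-group power is stated as nearly 80%, but 110 children per ethnic group gives about 46% to 55% for the BMI difference on the plan's own inputs

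*Protocol article*

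**What the plan says.** The Sample size section plans 330 children for at least 90% power to detect 0.8 kg/m² as the "difference in change in BMI from baseline to the end of intervention period between the two groups", "assuming a standard deviation (SD) of 2.0 kg/m^2", with a two-sided 5% test and "allowing for 20% loss to follow up". It adds that this size also gives at least 90% power for a VO2max difference of 3–5 ml/kg/min with SD 7. It then states that equal recruitment of Māori, Pacific and other children, 110 of each, "participants would provide nearly 80% power for the sub-group analysis under the same assumptions".

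The Statistical analysis section plans an analysis within each ethnicity if the overall treatment effect is significant, and premises it on balanced recruitment: "With roughly equal number of Māori, Pacific and non-Māori non-Pacific participants". The Discussion section on recruitment of indigenous and ethnic minority populations reports that, when the article was submitted, "the eGAME sample comprised 17% Māori and 27% Pacific participants, below the target of 33% for each".

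**The concern.** A sub-group holding one third of the children cannot keep close to 80% power for the same difference when the full sample was sized for 90%. The standard error within a third of the sample is √3 ≈ 1.73 times larger, which is far more than a ten-point loss of power can absorb.

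The figure supports the three-way recruitment target and the ethnicity-specific analyses. Suppose the overall effect is significant and the Māori or Pacific result is not. A reader who trusts the stated power may conclude that the intervention does not work in that group. In fact, a true effect of the planned size would be missed about half the time or more.

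**Working it through.** **Inputs** (Sample size section): difference d = 0.8 kg/m²; SD s = 2.0; two-sided α = 0.05; 20% loss; N = 330; 110 per ethnic group. The allocation ratio is not stated, so 1:1 is an assumption. It is supported by step 1.

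**Step 1. Reproduce the overall claim.** For two means, n per arm = 2(1.960 + 1.282)² s²/d² = 2 × 10.51 × 4/0.64 = 131.4, rounded up to 132. Allowing for loss, 264/0.8 = 330, an exact match. Power at 132 per arm is 90.1% (normal approximation) or 89.9% (t). This confirms the formula, the allocation and the way loss was handled.

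**Step 2. Apply the same inputs to one ethnic group.** 110 children make 55 per arm; after 20% loss, 44 per arm. Power ≈ Φ(d/(s√(2/n)) − 1.960).

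- n = 44: s√(2/44) = 0.426; 0.8/0.426 = 1.876; Φ(−0.084) = 46.7% (t: 45.8%).
- n = 55: s√(2/55) = 0.381; 0.8/0.381 = 2.098; Φ(0.138) = 55.5% (t: 54.7%).

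**Step 3. What 80% would take.**

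- Sample size: n per arm = 2(1.960 + 0.842)² × 4/0.64 = 98.1, so 99 analysed per arm, and 198/0.8 = 247.5, so 248 recruited per ethnic group.
- Detectable difference at 44 per arm: 2.80 × 0.426 = 1.19 kg/m² (1.21 by t). At the plan's mean height that is 1.19 × 1.58² ≈ 3.0 kg, against the roughly 2 kg assumed. At 55 per arm it is 1.07 kg/m².

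**Step 4. Other readings of the sentence.**

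| Reading | After 20% loss | No loss |
|---|---|---|
| BMI, two-sided 5%, as written | 46.7% | 55.5% |
| BMI, one-sided 5% | 59.1% | 67.5% |
| BMI, 110 taken as the number per arm | 75.6% (88 per arm) | 84.3% |
| VO2max 3 ml/kg/min, SD 7 | 52.0% | 61.3% |
| VO2max 4 ml/kg/min | 76.4% | 85.0% |
| VO2max 5 ml/kg/min | 91.8% | 96.3% |
| BMI, 0.8 contrast between the effects in two ethnic groups | 26.3% | 31.7% |

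Values are normal approximations; t values for the first six rows are up to about one point lower. Within the BMI calculation, taking 110 per arm comes close to the stated figure, but it would need 660 children. Omitting the factor 2 in the variance of a difference at 44 per arm also gives 75.6%. The document does not show whether either slip occurred.

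**Step 5. The reported mix, for illustration.** Assume the final 330 split 17/27/56% and lose 20%. Analysed numbers per arm are then 330 × 0.17 × 0.8/2 = 22.4, 330 × 0.27 × 0.8/2 = 35.6 and 330 × 0.56 × 0.8/2 = 73.9. BMI power by t is about 26%, 38% and 68%.

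**The case against.** The best defence is VO2max. The sub-group sentence follows directly on the VO2max statement and names no endpoint. At 44 per arm, a difference of 4 ml/kg/min gives about 76% and 4.2 gives about 80% (79.5% by t), both within the stated 3–5 range. So a figure near 80% can be reached with 110 children per group, but only for the upper part of that range. The sentence is not limited to VO2max, BMI is the primary outcome, and the overall claim of at least 90% does hold at 3 ml/kg/min (93.6% at 132 per arm). Held to that standard, the sub-group figure for VO2max is 51–52%.

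A second defence is that adjusting for baseline reduces the residual SD. To reach 80% it would have to fall from 2.0 to 1.34 after loss, or 1.50 without. The covariates would then have to explain 1 − (1.34/2.0)² ≈ 55% or 1 − (1.50/2.0)² ≈ 44% of the variance. The plan states no such reduction, and it would no longer be the same assumptions.

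Three further points stand as limits on the concern:

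- The sub-group analyses are done only after a significant overall effect, which narrows the setting in which a null ethnic result could mislead. It does not remove it: a null Māori or Pacific result beside a positive overall one is the case most open to misreading.
- The power sentence is conditional on equal recruitment, the article openly reports the shortfall, and the mix is interim. The figures in step 5 are therefore illustrative.
- The error leaves total sample size, randomisation and the primary analysis untouched.

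**Conclusion.** The concern holds. For BMI, the power within each ethnic group is about 46% with the planned 20% loss and 55% with none, against a stated figure of nearly 80%: a shortfall of roughly 25 to 34 points. This rests on 1:1 allocation, on 110 being the total per ethnic group across both arms, and on the plan's own difference, SD and two-sided 5% level. No two-sided 5% reading that keeps those BMI inputs comes near 80%. For VO2max the statement is true only from about 4.2 ml/kg/min upwards. The overall 90% claim is correct and unaffected.

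**What to change.** Replace the sub-group sentence in the Sample size section with wording such as: *With 110 children per ethnic group (44 per arm after 20% loss), power within each group to detect a 0.8 kg/m² difference in BMI change is about 46%; the difference detectable with 80% power is about 1.2 kg/m².* If a VO2max figure is kept, name the difference it refers to.

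Give the same figures for the ethnic mix actually recruited, since the Statistical analysis section still presumes near-equal groups. Describe the ethnicity-specific results as estimates with confidence intervals, so that a non-significant result in one group is not read as evidence of no effect.

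The cost is wording only: one stated figure becomes less favourable. Enrolment, design and the primary analysis do not change.

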### Intervention

The intervention involved an upgrade (hardware and games) of children's existing gaming technology to enable them to play the active video games at home. While various active video game systems exist (e.g., Dance Dance Revolution, Nintento Wii™, Sony EyeToy™) Sony EyeToy™ was used in the current study. This technology uses a USB motion-capture camera to place a picture of the gamer onscreen. The gamer then interacts with the images onscreen (Figure 1). The upgrade consisted of an EyeToy™ camera, dance mat, and a selection of active video games. Relationships were established with Sony Computer Entertainment (SCE) NZ (SCENZ) and Europe (SCEE), and SCEE provided the EyeToy™ cameras and software for the study.

**Figure 1 F1:**
[figure not shown]
**Example of child playing Sony EyeToy™ active video game**. Reproduced with permission from Sony Computer Entertainment Europe.

Current physical activity recommendations for children and adolescents are to perform 60-minutes of moderate to vigorous physical activity on most days of the week [38]. In the eGAME study, children were encouraged to meet these recommendations by (1) supplementing periods of inactivity with active video game play; and (2) to substitute periods of traditional inactive video game play with the active version. As compliance with the intervention has been highlighted as an issue in previous active gaming research, several reinforcement strategies were used to maximize compliance in this study. Firstly, the introduction of new games to participants was staggered to maintain interest and motivation (games were given at baseline and again at 12 weeks). Second, intervention participants were reminded at their follow-up assessments to continue playing the games. Children in the control group were asked to continue their normal video game playing and physical activity behavior. At the end of the study, the control group received the active video games upgrade package.

### Procedure

The principle method of recruitment was via schools. Primary (years 1–5), intermediate (years 6–7) and high schools (years 8–13) within the Auckland region were approached to participate in the study. Contact was made with the school principal in the first instance. If the principal agreed to be involved, a school presentation was scheduled, during which children were given brief information about the study. Recruitment also occurred via contacts with local church and community groups, after-school and school holiday programmes, and word of mouth. Interested children provided their contact details to study staff.

Following expression of interest, inclusion and exclusion criteria were assessed in a screening phone call with the child and their parent(s). If eligible, children were posted participant information and informed consent documentation, and booked to attend a baseline assessment. Eligible children attended assessments at a study site close to their place of residence. Four assessment sites were set up in community recreation facilities in the greater Auckland area.

Participants attended assessments at baseline, 12 weeks and 24 weeks, during which they completed a questionnaire assessing key psychological constructs related to physical activity behavior (intention, self-efficacy, perceived competence and enjoyment), had their height, weight and waist circumference measured, underwent bioelectrical impedance analysis (BIA) and completed a field test of physical fitness (20 meter shuttle test). Participants were then given an Actigraph accelerometer to wear for the following seven days to provide an objective assessment of free-living physical activity. During the same period, each participant completed a log-book, detailing their accelerometer wear, their video game (active and nonactive) use and the snack foods they had consumed. Study staff then visited participants at their homes to collect the accelerometer and completed log books.

It was not possible to blind participants to their experimental group allocation. However allocation concealment (up to the point of randomization) was maintained. It was also not possible to blind study staff administering interventions and assessing outcomes to experimental group allocation for pragmatic reasons.

